# Financial incentives to improve uptake of partner services for sexually transmitted infections in Zimbabwe antenatal care: protocol for a cluster randomised trial

**DOI:** 10.12688/wellcomeopenres.19199.2

**Published:** 2023-10-18

**Keywords:** Sexually transmitted infections, partner notification, incentive, point-of-care testing, antenatal care, pregnancy, Zimbabwe

## Abstract

**Introduction:**

Sexually transmitted infections (STIs) such as chlamydia, gonorrhoea, trichomoniasis, and syphilis, are associated with adverse birth outcomes. Treatment should be accompanied by partner services to prevent re-infection and break cycles of transmission. Partner services include the processes of partner notification (PN) as well as arranging for their attendance for testing and/or treatment. However, due to a complex mix of cultural, socio-economic, and health access factors, uptake of partner services is often very low, in many settings globally. Alternative strategies to facilitate partner services are therefore needed.

The aim of this study is to assess the impact of a small financial incentive on uptake of partner services for STIs as part of antenatal care (ANC) services in Zimbabwe.

**Methods and analysis:**

This trial will be embedded within a prospective interventional study in Harare, aiming to evaluate integration of point-of-care diagnostics for STIs into ANC settings. One thousand pregnant women will be screened for chlamydia, gonorrhoea, trichomoniasis, and syphilis. All individuals with STIs will be offered treatment, risk reduction counselling, and client PN. Each clinic day will be randomised 1:1 to be an incentive or non-incentive day. On incentive days, participants diagnosed with a curable STI will be offered a PN slip, that when returned will entitle their partners to $3 (USD) in compensation. On non-incentive days, regular PN slips with no incentive are provided.

The primary outcome measure is the proportion of individuals with at least one partner who returns for partner services based on administrative records. Secondary outcomes will include the number of days between index case diagnosis and the partner attending for partner services, uptake of PN slips by pregnant women, adverse birth outcomes in index cases, partners who receive treatment, and intervention cost.

**Registration:**

Pan African Clinical Trials Registry: PACTR202302702036850 (Approval date 18
^th^ February 2022).

## Introduction

Curable sexually transmitted infections (STIs) such as chlamydia, gonorrhoea, trichomoniasis, and syphilis, are associated with adverse outcomes in pregnancy
^
1
^. Unfortunately, globally rates of STIs remain high
^
1,
2
^. This is particularly true in Southern Africa where control of STIs is hampered by a limited availability of diagnostics, alongside other healthcare access and socio-cultural barriers
^
3
^.

Partner services are a crucial component of comprehensive case management for an STI in order to prevent re-infection of the index patient. This encompasses both partner notification (PN), whereby a sexual partner of an individual with an STI (the index case) is informed that they may be at risk of an STI, as well as ensuring their attendance for testing and/or treatment
^
4
^. However, the uptake of PN varies widely, and has not been widely implemented
^
5
^. When testing for chlamydia and gonorrhoea among young people in community settings in Harare, Zimbabwe, we found that only 8.8% (22/248) of partners returned to sites to receive treatment
^
6
^. This was using client referral, whereby the individual diagnosed with an STI is counselled and advised to inform their partners to return, often with the aid of a physical PN slip. This is the standard of care in Zimbabwe and many other settings
^
7
^. However, other strategies such as provider referral and expedited partner treatment have been used in different settings
^
4
^.

Provider referral refers to a strategy whereby it is the healthcare professional who informs the partner, which may be particularly helpful where the partner in question is a casual partner, whom the index patient may be reluctant to inform. Expedited partner treatment means that medication or a prescription is given directly to the index patient to be given to their partner. This may save time for both the healthcare provider and partner, but may face legal barriers unless specific laws authorising its use are in place
^
8
^. A systematic review of partner services in sub-Saharan Africa found that the proportion of notified partners who sought evaluation or treatment following client referral was 25% (range 0–77%) compared to 69% for provider referral and 84% for expedited partner treatment. Importantly, the figures for provider referral and expedited partner treatment in this review, were each based on a single study, demonstrating the limited data available to support these strategies
^
4
^.

Patients’ individual assessment of the risks and benefits of each PN method will vary with context. In antenatal care, one may assume that rates of PN would be better, potentially due to higher proportions of individuals in stable relationships, and the added consideration of ensuring the health of the baby, which may increase indexes’ motivation to inform their partner, and partners’ motivation to attend for treatment. However, several studies in pregnant women reveal a wide range of rates of completion of PN
^
4,
9–
12
^. This demonstrates that one must consider the broader set of facilitators and barriers to PN that will be unique to each individual. For example, risk of intimate partner violence must be particularly considered in pregnancy, with two-thirds of pregnant women in one study in Harare reporting a history of physical, sexual and/or emotional violence during pregnancy
^
4,
13
^.

Our experience with young people in Zimbabwe revealed that they found it very difficult to inform partners, and felt ill-equipped to have such conversations with their partners
^
6,
14
^. In particular, they had genuine concerns regarding their physical safety, with reports of violence noted
^
14
^. Furthermore, there are also social and emotional risks involved. In addition to potentially precipitating relationship breakdown, accusations of pre- or extra-marital relations may also be disseminated to family, friends or other community members, which may have an impact on an individual’s reputation
^
14
^. Appropriation of blame and spreading rumours were also raised by patients seeking care in Botswana
^
15
^. Overall, there was felt to be a “disconnect between the request to notify partners and the reality” of doing so, with the above challenges not being fully acknowledged
^
14
^. There are also important systems-level barriers to individuals seeking out any STI care, including availability and accessibility of services, with cost being a frequently mentioned barrier to access
^
3
^. These are all important factors when considering strategies to improve PN uptake. Although higher numbers of partners receiving treatment is optimal from an STI control perspective, individuals must not be exposed to unacceptably high levels of risk in order to achieve this.

This is particularly important for financial incentives, which have the potential to cause both benefit and harm. Incentives have been used in other settings to promote uptake and adherence to various health interventions. This includes improving uptake of HIV testing and result receipt, linkage to HIV treatment and voluntary medical male circumcision, and reducing high-risk sexual behaviour
^
16,
17
^. Choko
*et al.* (2021) investigated the use of partner-delivered HIV self-test kits, with and without financial incentives, in antenatal care in Malawi
^
18
^. Secondary distribution of test kits substantially increased HIV testing by male partners of pregnant women, by similar magnitudes with and without an incentive. Another study by Choko
*et al.* (2018) found that higher proportions of male partners of pregnant women were tested for HIV and linked into care or prevention, when the pregnant woman was provided with two HIV self-test kits for their partners and either a $3 incentive, $10 incentive, or phone reminder. However, no significant increase was noted when HIV self-test kits were provided alone
^
19
^.

A randomised controlled trial in Harare, Zimbabwe of both fixed and lottery-based incentives given to caregivers showed significantly increased HIV testing uptake among older children and adolescents
^
20
^. Another trial in rural Zimbabwe also demonstrated that small non-monetary incentives were associated with higher levels of couples’ HIV testing and counselling, and HIV case diagnosis
^
21
^.

There are fewer examples related to incentives for PN for STIs and a particular paucity of evidence from randomised controlled trials. In a qualitative study in Malawi, healthcare workers at an STI clinic felt that incentivising both partners and couples who attend together would have the greatest effect on improving treatment of partners
^
22
^. Another study in Malawi used a social contact recruitment programme to recruit social contacts (rather than partners) of individuals with STI syndromes (both with and without HIV), and community controls. Participants (“seeds”) were given coupons to give to their social contacts to come to the clinic for a health promotion visit, including HIV testing and counselling and STI syndromic screening, with seeds receiving $2 for each social contact successfully referred to the clinic. This study demonstrated that this was a feasible, effective and efficient method to identify individuals with undiagnosed HIV
^
23
^. 

Overall, incentives to improve uptake of PN for STIs have received insufficient attention to establish a clear evidence base regarding their use.

### Rationale

Partner notification has very low take-up in many settings globally. Alternative strategies to facilitate both index patients informing their partners, and particularly partners attending for treatment, must be considered to reduce reinfection, particularly for pregnant women. Incentives, financial or non-financial, to facilitate PN should be considered as a possible strategy. This approach has been used to promote uptake of other health interventions and could be programmed within services especially as it focuses on achieving a discrete outcome rather than requiring repeated engagement over time.

The rationale behind this intervention is that providing a financial incentive may specifically ameliorate some of the socioeconomic barriers that partners face in attending clinic for treatment, in particular transport costs. Importantly, it is not expected that this intervention will significantly influence the major barriers present for index cases to notify their partners in the first instance.

The aim of this study is to assess the impact of a small financial incentive on uptake of partner services for sexually transmitted infections within antenatal care services in Zimbabwe. It will also inform future studies related to partner services, in terms of feasibility and operationalisation of incentives.

## Protocol

### Study design and setting

A cluster randomised trial will be embedded within the “IPSAZ study” (Investigating point-of-care diagnostics for sexually transmitted infections and antimicrobial resistance in antenatal care in Zimbabwe), a prospective interventional study being conducted in urban primary healthcare clinics (PHCs) in Harare province, Zimbabwe, aiming to evaluate a strategy for integration of point-of-care diagnostics for STIs into ANC settings
^
24
^. Such PHCs provide routine nurse-led antenatal care.

### Study population and recruitment

Pregnant women will be consecutively enrolled into the IPSAZ study when attending a study clinic for routine ANC. The only exclusion criteria are prior enrolment into the IPSAZ study, or being unable or unwilling to provide written informed consent.

### Main study procedures

The procedures for the main IPSAZ study are described in detail in the main study protocol
^
24
^. In summary, in addition to HIV and syphilis testing provided as part of routine care, the IPSAZ study will provide on-site opt-out testing for chlamydia and gonorrhoea using Xpert® CT/NG assay (Cepheid), for trichomoniasis using OSOM® Trichomonas Rapid Test (Sekisui Diagnostics), and for Hepatitis B using the HBsAg 2 (Abbott Diagnostics Medical Co. Ltd). Comprehensive case management, including treatment and partner notification, will be provided as per national guidelines
^
7
^, ideally on the same day as sample collection. For participants unable to be treated on the same day, they will be contacted by telephone up to five times over 28 days, to advise them to return for treatment. For participants with symptoms, participants will be given the option to receive immediate syndromic treatment, or to receive tailored treatment following processing of their results.

All pregnant women will be contacted by telephone after birth, to collect data on birth outcomes. Alongside this, they will be asked if they notified their partners, if their partners were treated, and if there were any negative consequences of this, including verbal, physical, sexual, or other abuse, relationship breakdown, negative reactions from friends or other family members, or any other ramifications.

### Proposed intervention

As per standard of care, partners will be notified by client referral. Post-test counselling to participants diagnosed with an STI or treated for a syndrome will include the importance of partner treatment. They will be provided with PN slips for their partners to return for presumptive treatment. Index cases can receive as many PN slips as they require. Partners who attend the study clinic and present their PN slip will be provided with presumptive treatment free-of-charge. Partners will be considered lost-to-follow up if they have not returned within 28 days after treatment of the index case.

The intervention will be provision of $3 (USD) provided to a partner on returning to the clinic for treatment. The amount was based on in-depth interviews with pregnant women, male partners, and midwives, recruited when attending or working at one of the intervention clinics, as well as discussions with members of the intervention team. Questions on appropriate incentive value were embedded within broader discussions about PN, including different methods of PN, associated challenges, and feasibility of PN. Specifically for incentives, stakeholders were asked what they thought about the idea, any potential negative consequences, and what a suitable value would be for an incentive. Male partners often noted that an incentive should cover cost of travel, but also leave the partner with some additional money to spend. In contrast, pregnant woman and midwives tended to say any financial incentive, even very small, would prompt partners to attend. They also noted that unintended consequences could include using the incentive for alcohol or drugs, or for individuals who were not the index’s real partner to attend. A compromise value of $3 was therefore chosen, with a key factor being that $3 covers a return journey by public transport from the majority of locations from where pregnant women (and therefore potentially their partners) are likely to travel.

### Randomisation and blinding

Randomisation of each clinic day will be performed in a 1:1 ratio between days where issued slips are associated with an incentive and days where no incentive is issued. Randomisation by clinic day was chosen as a method to allocate incentives, in preference to individual randomisation, to prevent contamination. Additionally, if some individuals presenting on the same day were offered an incentive and others were not, this may lead to a greater perception of unfairness amongst participants.

Randomisation will be performed by a statistician not involved in the IPSAZ study, using the formula “=INT(RAND()*2)” in Microsoft Excel for each clinic day. Randomisation outcomes will be recorded on a document produced for each month, and kept at each clinic site. The intervention team will refer to this document to determine whether it is an ‘incentive’ or ‘non-incentive’ day. For each individual pregnant woman, it will also be documented whether an issued PN slip was associated with an incentive or not. Similarly, when partners return it will be recorded if an incentive was provided. To ensure compliance with the randomisation log, this data will regularly be cross-checked to ensure that clients are being provided the correct slip based on day of attendance.

It is not possible to blind participants or researchers to the intervention. However, participants will only be informed of the availability of an incentive once they test positive on an incentive day and have already informed the clinical team how many PN slips are required. This is to prevent participants from providing an artificially elevated number of partners in order for incentives to be provided to individuals who are not actual partners of the index case. Of note, women could still return with a male who is not a sexual partner, and this would be difficult to detect. However, given the factors discussed regarding ensuring the health of the baby, and that this would still require disclosure of treatment to another male, we feel that the risk of this is low.

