### Statistical analysis

Simple point estimates for each arm will be presented by calculating the number of participants given a PN slip for whom at least one partner returned to the study clinic for treatment divided by the total number of participants given a PN slip. This was chosen over a mean of cluster responses, due to the higher importance of giving equal weight to each individual, over that of each cluster. Analysis will be by intention-to-treat. Analysis per protocol will also be conducted as a sensitivity analysis, based on the type of PN slip that was recorded as being given.

Trial arms will be compared using individual-level logistic regression, using robust standard errors to account for any clustering. Robust standard errors will be used, over generalised estimating equations or random effects models, as the expected correlation within clusters is minimal. Results will be presented as per the CONSORT extension for cluster trials
^
34
^.

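### Upcoming day allocations are open to clinic staff, and the day that fixes a recalled woman's arm is not defined

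*Protocol article*

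**What the plan says.** Randomisation and blinding, protocol article:

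- The sequence is generated independently: "Randomisation will be performed by a statistician not involved in the IPSAZ study, using the formula" (an Excel coin toss per clinic day).
- The list then goes to the clinic: "Randomisation outcomes will be recorded on a document produced for each month, and kept at each clinic site". Staff delivering the intervention look up each day's type there.
- The arm is first described through slip issue: "Randomisation of each clinic day will be performed in a 1:1 ratio between days where issued slips are associated with an incentive". Later in the section, a woman hears of the incentive once she has a positive test on an incentive day. The compliance check asks whether "clients are being provided the correct slip based on day of attendance".
- Neither participants nor researchers are blinded. The woman learns of the incentive only after she has said how many slips she needs.

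Main study procedures: management is intended for the day of sampling where possible. Women not treated that day are telephoned up to five times over 28 days "to advise them to return for treatment".

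Statistical analysis: the comparison is by intention-to-treat among women given a slip. A per-protocol sensitivity analysis is "based on the type of PN slip that was recorded as being given".

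**The concern.** An independent statistician protects how the sequence is made, not who can see it. With a month of allocations on paper at the site, staff who look up today can also see the days to come, and the article describes no step that prevents this.

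That matters most where a woman's arm could still change after something is known about her. For a woman sampled, diagnosed and given slips on one day there is only one candidate day. For a recalled woman there are at least two, and the article does not say which one governs her slip type or her intention-to-treat arm. If it is the return day, her arm is settled by an appointment made after her result is known and while the calendar is visible. The slip cross-check would then pass the change as compliant, because the slip would match the day she came. Intention-to-treat protects a comparison only if the assigned arm is defined and fixed beforehand.

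**Working it through.** **The three anchors.**

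| Event that sets the arm | Woman managed the same day | Woman recalled |
|---|---|---|
| Day slips are issued | day 0 | return day |
| Day of positive test | day 0 | day of the result, which may precede the return |
| Day of attendance | day 0 | unclear: first visit or return visit |

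The three agree for same-day management and can disagree for recall. The article itself treats diagnosis and treatment as separate dates. Proposed intervention counts a partner as lost 28 days after the index case's treatment, while Outcomes counts 28 days from index diagnosis.

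**The plan's own figure.** Inputs from Sample size calculations: 300 index women (150 per arm), control rate 30%, alpha 0.05 (two-sided reproduces it), power 0.80, 1.5 women per cluster. A pooled-variance test of two proportions with 150/(1 + 0.5 × ICC) per arm gives a minimum detectable odds ratio of 1.958 at ICC 0 (stated 1.96) and 1.990 at ICC 0.10 (stated 1.99). The power figures are sound, and this point does not depend on them. They serve only as a yardstick.

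**Standard error under no effect.** √(2 × 0.30 × 0.70 / 150) = √0.0028 = 0.053, or 5.3 percentage points.

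**Steering scenarios (assumptions, not figures from the article).** Suppose no true effect and 30% return overall. Half the women have a likely-to-return partner (rate pH) and half do not (rate pL). A share r is recalled, and a share s of those is placed by type: likely returners on incentive days, the others on non-incentive days. The remainder split evenly. Arm sizes stay equal, and the share of likely returners is 0.5 + 0.5·r·s in the incentive arm and 0.5 − 0.5·r·s in control. The spurious difference is therefore r × s × (pH − pL).

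| r | s | pH / pL | Incentive v control | Difference | Odds ratio | Rejection rate at nominal 5% |
|---|---|---|---|---|---|---|
| 10% | half | 40% / 20% | 30.5% v 29.5% | 1 point | 1.05 | 5.4% |
| 10% | half | 50% / 10% | 31% v 29% | 2 points | 1.10 | 6.7% |
| 20% | half | 40% / 20% | 31% v 29% | 2 points | 1.10 | 6.7% |
| 20% | half | 50% / 10% | 32% v 28% | 4 points | 1.21 | 11.8% |
| 30% | all | 40% / 20% | 33% v 27% | 6 points | 1.33 | 20.6% |
| 30% | all | 50% / 10% | 36% v 24% | 12 points | 1.78 | 62.8% |

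The last row is close to the odds ratio the trial can detect (1.96). The first is well inside the noise. The article gives no recalled share, so nothing in it places the trial within this range.

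**The case against.** Several safeguards are real. Enrolment is consecutive at routine antenatal visits with few exclusions, and test results come after enrolment, so steering at entry has little purchase. Slip numbers are stated before the woman hears of the incentive. The primary outcome needs only one returning partner, so extra slips would change little. Slip type is recorded and checked against the log. Same-day management is the aim, so the exposed group may be small, and with 10% recalled and half steered the test stays near its nominal level. Detailed procedures are also deferred to the main study protocol, which may define the governing day. All of this stands. It narrows the exposure to recalled women, but it does not conceal the list or reconcile the three anchors that this article states.

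A reader might go further in three ways that the text does not support.

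- That one team enrols, counsels and recalls. The article has the intervention team consult the list and, in the Discussion, support women's decisions. It does not say who enrols women or makes the calls.
- That there is no concealment at all. It is lacking towards staff. Participants are kept unaware until after the result and the slip count.
- That the per-protocol analysis regroups women by the slip received. The wording allows that, but excluding mismatched women fits it equally well.

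**Conclusion.** The point holds in a limited form. Upcoming allocations are not concealed from clinic staff, and the arm of a recalled woman is not tied to one defined day. Her intention-to-treat arm can therefore depend on a return date set with her result and the calendar in view.

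The size is unknown. Under the assumed scenarios it runs from negligible (odds ratio 1.05 to 1.10, or 1 to 2 points) to material (1.33 to 1.78, or 6 to 12 points), against a standard error of 5.3 points. The upper end needs 30% recalled and every one of them steered by likely response.

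It would be wrong to infer that steering will happen or that the trial is biased: the documents show an opening, not its use. This is a cheap improvement rather than a defect that invalidates the design.

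**What to change.** 1. **Conceal the list.** The independent statistician or a data manager holds it off site. Each day's arm is released only on that day, once the first woman due a slip has stated her slip number. The trigger should cover women due a slip by test result or by syndrome, because women treated for a syndrome also receive slips and need no positive test.
2. **Fix the arm.** Define each woman's arm and cluster for intention-to-treat by the date of sample collection at enrolment. Use the same date for the slip cross-check and for slip type at recall. Report the number recalled by arm.
3. **Define the per-protocol set.** State that it excludes women whose slip type does not match that arm and does not regroup them.

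Costs: there is one extra step per day, and later women on a day follow an arm already revealed. When a recalled woman returns, both slip types may occasionally be issued on one day. That slightly erodes the contamination and fairness reasons given for randomising by day.

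If mixed slips on a day are unacceptable, apply the sample-date rule to the analysis only and let slip type follow the return day. This does not allow steering between arms, but it dilutes the contrast. If return days are unrelated to the sample-day arm, recalled women contribute no difference and any true effect shrinks by a factor of about 1 − r: 0.90 if 10% are recalled, 0.70 if 30% are. The loss is slight only if few are recalled.

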### Outcomes

The primary outcome measure is the proportion of indexes with at least one partner who returns to the study site for partner services within 28 days of index diagnosis. Each PN slip will also have a unique ID that links partners to the index client, thus allowing for recording of this data. The main secondary outcome will be the number of days between index case diagnosis and the partner attending for partner services. Additional secondary outcomes will include uptake of PN slips by pregnant women, adverse birth outcomes in index cases, number of partners who receive treatment, and intervention cost. Number of partners who receive treatment will be recorded from our study antibiotic administration records, and compared with that reported by participants during telephone follow-up.

Furthermore, the proportion of indexes with at least one partner who returns to the study site for partner services any number of days from index diagnosis, will also be measured as a secondary outcome.

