### Process evaluation

An accompanying mixed methods process evaluation will be conducted to further understand the PN process and the influence of incentives on uptake, within the broader IPSAZ study process evaluation, described in the main study protocol
^
24
^. This process evaluation follows the MRC process evaluation framework, with research domains including fidelity, coverage, responses to and interactions with the intervention, interactions and consequences, and context. Key aspects relevant for PN and this trial are feasibility, acceptability to both pregnant women and partners, how incentives influence interactions between the index case and their partners, and unanticipated pathways or consequences. Of note, assessments of acceptability will explore comparisons between standard PN, incentivised PN, and also no PN, which may be the most acceptable option for some participants. Methods include; in-depth interviews and focus group discussions with pregnant women, healthcare workers, members of the intervention team, and male partners; unstructured observations; and routine monitoring data. Unstructured observations will be of clinical encounters and will be conducted by a research assistant not involved with delivery of the intervention. As observation may impact consultations, permission will be requested from participants, confidentiality will be re-assured, and the research assistant will aim to be as unobtrusive as possible. Interviews with pregnant women and partners will be conducted after PN has been attempted or completed, in order to assess for unintentional consequences or adverse outcomes. As previously mentioned, negative consequences of PN will be documented during a post-natal telephone call.

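### The protocol rules out blinding for all researchers, but post-natal telephone callers need not know which slip a woman received

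*Protocol article*

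**What the plan says.** The section Randomisation and blinding states: "It is not possible to blind participants or researchers to the intervention". It makes no exception for any role. The one safeguard it then describes concerns when women learn of the incentive: "participants will only be informed of the availability of an incentive once they test positive on an incentive day", and after they have said how many slips they need. The same section shows who uses the allocation in daily work: "The intervention team will refer to this document to determine whether it is an ‘incentive’ or ‘non-incentive’ day".

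Main study procedures describes a later contact: "All pregnant women will be contacted by telephone after birth, to collect data on birth outcomes". In the same call, "they will be asked if they notified their partners, if their partners were treated, and if there were any negative consequences of this", with several forms of abuse and relationship breakdown among the consequences listed. The article does not say who makes the call or whether that person can see the slip type.

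On data sources, the abstract defines the primary outcome as the proportion of individuals with "at least one partner who returns for partner services based on administrative records". Under Outcomes, the number of partners treated comes from the study's antibiotic records and is then "compared with that reported by participants during telephone follow-up". Adverse birth outcomes are listed there as a secondary outcome.

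**The concern.** Not being able to hide a cash payment from those who give and receive it does not mean that nobody can collect data without knowing the arm. The sentence treats the two as the same and so gives up a safeguard for the one data source where interviewer behaviour matters.

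Three uses of the call are at stake.

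- **Harm.** The Introduction says financial incentives may do harm as well as good, and the Discussion raises coercion and violence. The call is the routine source, covering every participant, for abuse and relationship breakdown. Answers to such questions depend on how they are put, and a caller who knows the arm may probe more or less in one arm.
- **Interpretation of the primary result.** The Discussion accepts that some partners may be treated at another clinic and so be missed. The payment is made only on return to the study clinic, so it could change where partners go as well as whether they go. The woman's telephone report of partner treatment is a natural check on this, and it is less useful if it is elicited differently by arm.
- **Birth outcomes.** This is the listed secondary outcome that clearly rests on the call.

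**Working it through.** This is mainly a reading of the text; no figure in the protocol bears on blinding.

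**1. The plan's own design figure.** For 150 index women per arm (100 clusters × 1.5), a control proportion of 30%, ICC zero and two-sided alpha 0.05, an odds ratio of 1.96 gives an intervention proportion of (1.96 × 0.30/0.70) / (1 + 1.96 × 0.30/0.70) = 0.84/1.84 = 0.4565. The two-proportion formula with pooled variance under the null then gives power 80.1%, and solving for 80% gives 1.958. The stated 1.96 reproduces. It concerns the primary outcome, and masking callers does not change it.

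**2. Who needs the allocation to do the task.**

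| Task | Needs slip type? | Basis in the article |
|---|---|---|
| Issuing slips | Yes | The intervention team consults the monthly document |
| Paying returning partners | Yes | The payment is the intervention |
| Receiving a slip or payment | Known to the recipient | Open intervention |
| Post-natal call | No | No listed item refers to the incentive |

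**3. Whether the call depends on the arm.** All enrolled women are called. On the planning figures, 1000 women × 30% = 300 receive slips, so about 1000 − 300 = 700 have no slip at all. The call must therefore work without a slip type. For the 300, the caller needs to know at most that a slip was given, so that the partner questions are asked.

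**4. Which results depend on the call.**

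| Item | Source | Open to caller influence? |
|---|---|---|
| Primary outcome | Administrative records, linked by slip ID | Largely no |
| Days to partner attendance | Date of attendance | Largely no |
| Partners treated | Antibiotic records | Largely no; only the comparison figure comes from the call |
| Slip uptake, cost | Clinic and cost data | No |
| Adverse birth outcomes | Call | Yes |
| Notification, abuse, relationship breakdown | Call; not listed under Outcomes | Yes |

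**5. Illustration on assumed inputs.** None of these inputs is in the document. Let an event have the same true rate t in both arms, and let callers elicit it with sensitivity s1 in one arm and s2 in the other. The spurious odds ratio is [t·s1/(1 − t·s1)] / [t·s2/(1 − t·s2)].

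- t = 0.10, s1 = 0.90, s2 = 0.80: (0.09/0.91)/(0.08/0.92) = 1.14.
- t = 0.10, s1 = 0.90, s2 = 0.70: (0.09/0.91)/(0.07/0.93) = 1.31.
- Over t from 0.05 to 0.30, the ranges are 1.13 to 1.17 (90% against 80%) and 1.30 to 1.39 (90% against 70%).

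This shows the direction and scale of such a bias if it occurred. It is not evidence that it will occur.

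**The case against.** The best defence is that the sentence, read in context, says only that an openly paid incentive cannot be hidden from those who give and receive it. It stands between text on the team consulting the day list and text on when women are told. The call belongs to the main IPSAZ study, whose procedures are set out in a separate protocol that is not shown; callers may already be separate from the clinic team, and a script may exist. That is a fair reason to keep the point minor. It does not rescue the wording, which excludes blinding for researchers without exception.

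It is also true that women know their arm, that questions about partners invite them to mention the payment, and that their own reporting bias would remain. The bias is therefore reducible, not avoidable.

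A reader might go further in four ways that the document does not support.

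- **That the trial's main comparison is at risk.** It is not, given the record-based sources.
- **That the analyst should be covered by the same point.** Masking an analyst guards against analysis choices and cannot protect data already collected by telephone. Such arrangements are commonly left to an analysis plan, which is not shown.
- **That an inflated false-positive rate can be quoted.** That would require an assumed shift in reporting and a between-arm test of harms or self-reported notification. The Statistical analysis section describes no such test.
- **That masked staff are already in place.** Under Process evaluation, the observations "will be conducted by a research assistant not involved with delivery of the intervention". That assistant watches clinical encounters, is not said to be unaware of the arm, and is not said to make calls.

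**Conclusion.** The point holds as a minor one and is best labelled a cheap improvement. The categorical statement is wrong for the post-natal callers, and correcting it would reduce interviewer bias in birth outcomes, in self-reported notification and partner treatment, and above all in reports of abuse and relationship breakdown. No numerical size can be given from the document; the odds ratios in the illustration rest wholly on assumed sensitivities.

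The conclusion assumes that the call contains only the items the article lists and that the main study protocol does not already keep callers unaware of the arm. If it does, only the sentence needs correcting.

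**What to change.** 1. Reword the sentence so that the impossibility of blinding applies to participants and to staff who issue or redeem slips, and state that post-natal callers will work without knowledge of the arm.
2. Give callers a list that omits slip type; it may show that a slip was given. Keep the monthly allocation document from them, because the visit date and that document together reveal the arm.
3. Where possible, assign each call to an existing member of staff who did not issue that woman's slip.
4. Ask the notification, partner-treatment and harm questions from a fixed script, the same in both arms.
5. Have the caller record whether the arm became known during the call.

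The cost is one protocol sentence, a list exported without one column, a short script and minor rostering. Sample size, power and the primary analysis do not change. Some women will still reveal their arm, and step 5 shows how often.
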